### Sample size calculation

Sample size and power calculations were performed for the main outcome of interest - difference in mean HbA1c levels - using effect sizes and standard deviations derived from multiple published trials of patient-education interventions. The recent meta-analysis by Deakin et al. of 11 such studies found a mean difference in HbA1c of 0.8% [14]. Analysis of Family Health Center patients with HbA1c values 8.0% or higher showed a standard deviation of 1.9. Using a conservative assumption of an effect size of 0.6 for percent HbA1c, we would need 180 subjects in each arm to achieve a power of .85 using the standard threshold for a significant difference of .05 (2-sided). To account for a 10% loss to follow-up, we will enroll 200 subjects in each arm.

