### Data analysis

Initial analyses will compare the frequency of baseline levels of outcome and other key variables (e.g., demographic and disease characteristics) for the two groups using a simple chi-square test (for categorical variables), t-test (for continuous variables with an approximately normal frequency distribution) and the Mann-Whitney-U test for continuous, non-normally distributed variables. Evaluation of intervention effectiveness will be by intention to treat using the above statistical tests. Evidence of clustering by clinic site and primary care provider will be examined and adjusted for analyses as needed. If significant differences in baseline characteristics are found, analyses will be repeated adjusting for these differences using ANOVA and logistic regression for multivariate analyses. Sensitivity analyses will be performed to estimate the effects of missing data using different assumptions (e.g., imputed values). Additional analyses will be conducted to look for evidence of effect modification by pre-specified subgroups: baseline HbA1c (< median, > median) and by English as primary language (Y/N).

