### Outcome measures

Outcomes variables are measured at baseline and at 6 months. Peer coaches are assessed at 12 months. The primary outcome is change in HbA1c. Secondary outcomes include change in: systolic blood pressure, BMI, LDL, diabetes self-care activities, medication adherence, diabetes-related quality of life, diabetes self-efficacy, and depression.

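### Baseline HbA1c becomes a covariate only after a positive baseline significance test; fixing ANCOVA in advance would gain precision at no cost

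*Protocol article*

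**What the plan says.** Outcome measures defines the endpoint: "The primary outcome is change in HbA1c", with measurements at baseline and 6 months.

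Data analysis begins by testing baseline levels of the outcome and other key variables between the arms, using chi-square, t or Mann-Whitney tests. The treatment comparison then uses the same tools: "Evaluation of intervention effectiveness will be by intention to treat using the above statistical tests". Baseline HbA1c therefore enters the main comparison only by subtraction, not as a covariate. Covariate adjustment follows a conditional rule: "If significant differences in baseline characteristics are found, analyses will be repeated adjusting for these differences". ANOVA and logistic regression are the methods named for it. No sentence ranks the adjusted result against the unadjusted one.

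Sample size calculation works on a different scale, the "main outcome of interest - difference in mean HbA1c levels", and takes no credit for covariate adjustment.

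**The concern.** Allocation is random, so a significant baseline difference reflects chance. The test does not ask whether adjustment is useful. That depends on how strongly the variable predicts the outcome, and a strongly prognostic variable is worth adjusting for even when its imbalance is not significant. Baseline HbA1c is the obvious candidate for 6-month HbA1c, yet under this rule it becomes a covariate only in the few trials where its own test is positive.

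Two things are at stake. One is precision: an unadjusted change score is less precise than ANCOVA unless the regression of 6-month on baseline HbA1c happens to have slope 1. The other is clarity: when the trigger fires there are two estimates and no stated order between them, in a trial that is unblinded.

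**Working it through.** **Inputs from Sample size calculation.** Difference 0.6: "Using a conservative assumption of an effect size of 0.6 for percent HbA1c". SD 1.9: "Analysis of Family Health Center patients with HbA1c values 8.0% or higher showed a standard deviation of 1.9". Size and power: "we would need 180 subjects in each arm to achieve a power of .85". Two-sided alpha 0.05.

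**Assumed.** The baseline to 6-month correlation r is not in the documents; the range 0.3 to 0.7 is used. The SD is taken as 1.9 at both times. The baseline test is taken as a t-test at 0.05, since the section sets no level for it.

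**Step 1, the plan's own figure.** n = 2(1.96 + 1.036)² × 1.9² / 0.6² = 2 × 8.98 × 3.61 / 0.36 ≈ 180.1, or 181 rounded up (181.03 with the t distribution). Power at 180 per arm is 0.850. 180 / 0.9 = 200. The plan's figures reproduce and are not in dispute.

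**Step 2, variance and power.** Change-score SD = 1.9√(2(1−r)). ANCOVA residual SD = 1.9√(1−r²). The variance ratio is (1−r²) / (2(1−r)) = (1+r)/2. Power = Φ(0.6 / (SD√(2/180)) − 1.96).

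| r | Change SD | Power, change | ANCOVA SD | Power, ANCOVA | Variance ratio |
|---|---|---|---|---|---|
| 0.3 | 2.248 | 0.716 | 1.812 | 0.881 | 65% |
| 0.5 | 1.900 | 0.850 | 1.645 | 0.933 | 75% |
| 0.7 | 1.472 | 0.972 | 1.357 | 0.987 | 85% |

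For power 0.85, the change score needs 253, 181 and 109 per arm; ANCOVA needs 164, 136 and 92.

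**Step 3, sensitivity to equal SDs.** Suppose the 6-month SD is 1.2 times baseline and r = 0.5 (assumed). In units of baseline variance, the change score has 1 + 1.44 − 2 × 0.5 × 1.2 = 1.24 and ANCOVA has 1.44 × 0.75 = 1.08. The ratio is 0.87, a gain of 13% rather than 25%. A 6-month SD below baseline would make the gain larger than 25%.

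**Step 4, imbalance the trigger lets through.** SE of the baseline difference = 1.9√(2/180) = 0.200, so anything up to 1.96 × 0.200 = 0.39 points is non-significant. Given an imbalance, the change-score estimate shifts by (1−r) times its size.

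- Edge of the 95% range (0.39): 0.24 at r = 0.4 and 0.20 at r = 0.5, a third or more of the 0.6 target.
- Median chance imbalance (0.67 × 0.200 ≈ 0.135): 0.08 at r = 0.4 and 0.07 at r = 0.5, roughly an eighth of the target.

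**Step 5, does the trigger recover the loss or distort error rates?** This was simulated with 20,000 trials per scenario at 180 per arm, letting the adjusted result replace the unadjusted one whenever the HbA1c baseline test was positive.

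- The baseline test was positive in about 5% of trials.
- Power at r = 0.5 was 0.855 with the change score as the default, against 0.929 for ANCOVA in every trial.
- Overall type I error under the rule was 0.034 to 0.049 across r of 0.3, 0.5 and 0.7, with either change or 6-month level as the default. It is not inflated.
- Within the trials with a positive baseline test, the unadjusted change test had conditional type I error of 0.267, 0.163 and 0.122 at r = 0.3, 0.5 and 0.7.

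**The case against.** The strongest defence is that nothing here is invalid. The intention-to-treat comparison is unconditional, and after a positive baseline test the analyses are repeated, not replaced. A reader might infer that the effectiveness estimate itself depends on a chance pre-test. The text does not support that: the unadjusted estimate exists either way, and only the existence and covariates of an additional adjusted run depend on the test. That estimate is unbiased over randomisations, and its standard error already allows for chance imbalance. The shifts in step 4 are conditional on a realised imbalance, and the larger pair belongs to the edge of the range. The raised conditional error in step 5 arises in just those trials where the plan adds an adjusted analysis. All of this stands.

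A reader might also infer that power built into the sample size is thrown away. It is not. The calculation assumed an unadjusted comparison with SD 1.9, and at r = 0.5 the change score delivers exactly the planned 0.850. The shortfall below r = 0.5 arises because the trial is sized on levels while the primary outcome is change. That is a separate matter from the trigger, although ANCOVA would cure it across the range examined.

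Nor should much be made of ANOVA being named rather than ANCOVA; in a condensed article it may be shorthand for linear models. There is likewise no basis here for demanding clinic and language as fixed covariates, since the enrolment section describes no stratification by either.

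The defence does not rescue the trigger. It is a rule the article states, not a detail left to another document. An unshown analysis plan may rank the two results, so the missing order is the lesser part of the point.

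**Conclusion.** The point holds as one of efficiency and clarity. The plan makes adjustment for a probably prognostic baseline value depend on a test that detects only chance, and it leaves the order of two possible results unstated. With equal SDs, the precision forgone is 35%, 25% or 15% of the change-score variance at r = 0.3, 0.5 or 0.7. In power at 180 per arm this is about 16, 8 or 1.5 percentage points. The trigger recovers almost none of it (0.850 to about 0.855 at r = 0.5). The size depends on a correlation and a 6-month SD that the documents do not give. The direction does not: in large samples ANCOVA is never less precise than the unadjusted change score. This is an improvement available for free, not a defect that must be corrected for the trial to be valid.

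**What to change.** In Data analysis:

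- Name one primary analysis: ANCOVA of 6-month HbA1c (or of change, which gives the same treatment effect) on arm, with baseline HbA1c as a continuous covariate, whatever the baseline comparison shows.
- Treat each continuous secondary outcome in the same way, with its own baseline value as covariate.
- Delete the sentence that triggers adjustment by baseline significance tests, and keep the baseline comparison descriptive.
- Label any unadjusted analysis as supportive.

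The cost is wording only. Outcome variables are already measured at baseline, and the sample size need not change.

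### The baseline-HbA1c subgroup rule leaves patients at the median unassigned, and a median split discards a third to a half of the information if the effect varies roughly linearly with HbA1c

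*Protocol article*

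**What the plan says.** The Data analysis section of the protocol article closes with a subgroup plan: "Additional analyses will be conducted to look for evidence of effect modification by pre-specified subgroups". The two modifiers are given as "baseline HbA1c (< median, > median) and by English as primary language (Y/N". The section names no interaction test or model for this, does not mention treating baseline HbA1c as continuous, and does not say where a patient at the median belongs.

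The outcome is continuous: "The primary outcome is change in HbA1c" (Outcome measures). The Sample size calculation section supplies the other inputs. On variability it reports: "Analysis of Family Health Center patients with HbA1c values 8.0% or higher showed a standard deviation of 1.9". The difference to be detected is set at 0.6 percentage points, tested two-sided at 0.05. The resulting requirement is stated as "we would need 180 subjects in each arm to achieve a power of .85". Enrolment is then raised to 200 per arm to allow for one patient in ten being lost. The sizing covers the overall difference in mean HbA1c only.

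**The concern.** Pre-specifying a subgroup should fix its membership before anyone sees the data. With two strict inequalities, a patient at the median falls in neither group, and the analyst must decide later what to do. HbA1c is a coarsely recorded measure, so such ties are likely.

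Baseline HbA1c is also a continuous modifier. Reducing it to two halves treats a patient just above the median like one far above it. If benefit grows gradually with baseline HbA1c, much of the evidence for that is thrown away, in an analysis that has little power to begin with. The cut-point is set by whoever enrols, so the subgroup result is harder to read in another clinic population than an effect per HbA1c point would be.

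**Working it through.** **1. The plan's own figure.** Difference 0.6, SD 1.9, two-sided 0.05, power 0.85:

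n per arm = 2 × (1.960 + 1.036)² × 1.9² / 0.6² ≈ 180.1, which rounds up to 181 (182 with the t distribution). Power at 180 per arm is 0.850 (0.848 with t). 180 / 0.9 = 200. The stated 180 and 200 reproduce.

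**2. Power left for a split interaction.** With 360 analysed, each arm-by-half cell has 90 patients.

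- SE of the main effect: 1.9 × √(2/180) = 0.20.
- SE of the interaction: 1.9 × √(4/90) = 0.40, twice as large.
- A between-half difference of 0.6, as large as the whole assumed effect: 0.6 / 0.40 = 1.50, power about 32%.
- Difference needed for 85% power: (1.960 + 1.036) × 0.40 ≈ 1.2.

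**3. Information kept by the split.** Under a linear gradient this is the squared correlation between baseline HbA1c and its above-median indicator. The shape of the baseline distribution is not in the documents, so three were used, each with SD 1.9: normal 0.64 (that is, 2/π), 8 + gamma 0.55, 8 + exponential 0.48. The loss is therefore 36% to 52%. Entry at about 8% makes right skew plausible, which points to the larger losses.

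**4. Simulated power.** 3,000 trials per scenario, 360 patients, outcome SD 1.9, baseline rounded to 0.1%. Assumed modification: a linear gradient of 0.6 per baseline SD, or a step giving a 1.2 difference between halves.

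| Baseline shape | Linear: continuous | Linear: strict split | Step at median: continuous | Step at median: strict split |
|---|---|---|---|---|
| Normal | 84.5% | 66.5% | 65.2% | 83.1% |
| Gamma | 84.9% | 61.6% | 61.0% | 83.5% |
| Exponential | 83.0% | 52.7% | 54.8% | 84.1% |

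With no modification, both tests rejected in about 5% of trials.

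Algebra agrees for the linear case. The continuous test has noncentrality 0.6 / (1.9 × 2/√360) = 3.00, hence power 85%. Multiplying by √0.64, √0.55 and √0.48 gives about 67%, 60% and 55% for the split.

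**5. Patients at the median.** On average 7.5 to 9.4 of 360 (2.1-2.6%), at most 22. Under the linear gradient, assigning them by an at-or-above rule gave power of 49.8-65.4%, against 52.7-66.5% without them. The loss comes from dichotomising, not from the ties.

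**6. Sensitivity to the gradient.** With a gamma-shaped baseline, residual SD 1.7 and a gradient of 0.3 per HbA1c point, power was about 0.87 continuous against 0.61 split. That gradient equals 0.3 × 1.9 = 0.57 per baseline SD, nearly the whole assumed main effect. At 0.15 per point, power was 0.34 against 0.19.

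**7. Sensitivity to unequal variance.** Let the residual SD be 1.2 + 0.25 per point above 8 (an assumption), with no true modification. Ordinary least squares on the continuous interaction then rejected in 19% of trials and the median split in 5.5%. Robust standard errors brought the continuous test to about 6%, but removed its power advantage in that scenario.

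**The case against.** The strongest case against has four parts.

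- **Ties.** A reader might infer that the plan excludes patients at the median. The text never says so. The two signs may be shorthand in a condensed article, which uses inequality signs loosely elsewhere: patient entry is at or above 8% under Eligibility criteria but above 8.0% under Identification and recruitment. This stands. What remains is an unassigned category of about 2-3%, with no material power cost.
- **Power.** A reader might also infer that the continuous interaction is always more powerful. It is not: the order reverses for a step at the median, and with a modest gradient neither test is adequate. This stands as a condition. It does not remove the point, because a step exactly at a value set by who enrols is less plausible than a gradient.
- **Side effects.** On a skewed baseline, the slope leans on a few high values, and ordinary standard errors can mislead if variance rises with baseline. This stands and shapes the fix.
- **Fit with the plan.** The article's main comparison is a t-test or Mann-Whitney test, with ANOVA or logistic regression only if baseline differences appear. There is no primary regression to which an interaction could simply be added. This stands, so the model has to be written out.

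The argument that a sample median cannot be carried to other populations is weak, since the observed median can be reported with the result. Nor can the whole matter be left to an unseen analysis plan: the article itself fixes the split.

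**Conclusion.** The concern holds in a limited form and is minor. As written, the rule leaves patients at the median without a subgroup, about 2-3% if HbA1c is recorded to 0.1%; that is a wording gap. The substantive weakness is the split, which discards roughly a third to a half of the information if the effect varies roughly linearly with baseline HbA1c. For a gradient of 0.6 per baseline SD, this means power of 53-67% instead of 83-85%.

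These sizes rest on assumed baseline shapes, a baseline SD equal to the quoted 1.9, constant residual variance and a large gradient. With a smaller gradient both tests are weak. These are additional analyses: the primary comparison and sample size do not depend on them, and a null finding from either method would say little.

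**What to change.** Replace the baseline-HbA1c part of the subgroup sentence with: *Effect modification by baseline HbA1c is tested by the treatment × baseline HbA1c (continuous) interaction in a linear regression of 6-month change in HbA1c on treatment, baseline HbA1c and their product, with heteroscedasticity-robust standard errors and a check for non-linearity; effects are also shown for ≤ median versus > median, with the observed median reported.* State that the analysis is exploratory. The language subgroup is already binary and can stay as it is.

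The cost is one sentence and one extra model, with no new data. The downside is small but real: the continuous test is less powerful than the split if the effect is a step near the median, and its advantage can disappear if residual variance rises strongly with baseline. The non-linearity check and the ≤ / > display help a reader recognise a step.

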### Outcome measures

Outcomes variables are measured at baseline and at 6 months. Peer coaches are assessed at 12 months. The primary outcome is change in HbA1c. Secondary outcomes include change in: systolic blood pressure, BMI, LDL, diabetes self-care activities, medication adherence, diabetes-related quality of life, diabetes self-efficacy, and depression.

### Qualitative evaluation

The peer coaches will voluntarily participate in a focus group, semi-structured interviews, or both, to assess how they experienced the training and coaching process. The focus group is designed to reveal the coaches' general attitudes and facilitate the development of the interview guide. Semi-structured interviews, between 40-75 minutes in length, are conducted in either English or Spanish. Coaches are prompted to discuss their efficacy as coaches, the training experience, the impact of coaching on their management of their own diabetes, and their role in the health care team.

The focus group and interviews are audio recorded and transcribed. Using methods based on grounded theory, as described by Miles and Huberman, transcripts are encoded and organized to identify, develop and analyze themes [15].

## Discussion

Self-management training and support is an effective component of care for people with diabetes. Due to a shortage of time and resources, this critical support is not consistently delivered in most health care settings. The current study uses trained patients to provide this support. Facing the same struggles as the patients they coach, trained peer coaches can assist the health care team to deliver the recommended National Standards for Diabetes Self-Management Education [16].

In our study, we pair trained patients with better-controlled diabetes and patients with poorly controlled diabetes to provide one-on-one self-management support. Coaches are trained to: provide information about diabetes and healthy lifestyle choices pertaining to physical activity and nutrition; help patients with medication understanding and adherence; and work collaboratively with patients to create actions plans around behavior and lifestyle changes. Coaches and patients speak bi-weekly, meet face-to-face at least twice during the course of the 6 month intervention, and coaches are encouraged to attend the patient's clinical visit.

We hypothesize that patients in the intervention arm with a peer health coach will show significant improvements in the clinical indicators pertinent to diabetes (HbA1c, LDL cholesterol and blood pressure), diabetes self-efficacy, and self-care activities compared to patients in the control arm. In addition, we anticipate that trained peer coaches will demonstrate similar significant improved outcomes.
